[figure not shown]

**LIST OF ABBREVIATIONS AND RELEVANT DEFINITIONS**

|                |                                                                                                                                                                                                                                                                                                                                                  |
|----------------|--------------------------------------------------------------------------------------------------------------------------------------------------------------------------------------------------------------------------------------------------------------------------------------------------------------------------------------------------|
| ABR     | ABR form (General Assessment and Registration form) is the application form that is required for submission to the accredited Ethics Committee (ABR = Algemene Beoordeling en Registratie)                                                                                                                                                |
| AE      | Adverse Event                                                                                                                                                                                                                                                                                                                             |
| AR      | Adverse Reaction                                                                                                                                                                                                                                                                                                                          |
| CA      | Competent Authority                                                                                                                                                                                                                                                                                                                       |
| CCMO    | Central Committee on Research Involving Human Subjects                                                                                                                                                                                                                                                                                    |
| CTCM    | Clinical Trial Centre Maastricht                                                                                                                                                                                                                                                                                                          |
| DSMB    | Data Safety Monitoring Board                                                                                                                                                                                                                                                                                                              |
| EU      | European Union                                                                                                                                                                                                                                                                                                                            |
| EudraCT | European drug regulatory affairs Clinical Trials GCP Good Clinical Practice                                                                                                                                                                                                                                                               |
| IB      | Investigator's Brochure                                                                                                                                                                                                                                                                                                                   |
| IENF    | Intraepidermal nerve fiber                                                                                                                                                                                                                                                                                                                |
| METC    | Medical Research Ethics Committee (MREC); in Dutch: Medisch Ethische Toetsing Commissie (METC)                                                                                                                                                                                                                                            |
| PI      | Principal Investigator                                                                                                                                                                                                                                                                                                                    |
| (S)AE   | (Serious) Adverse Event                                                                                                                                                                                                                                                                                                                   |
| SPC     | Summary of Product Characteristics (in Dutch: officiële productinformatie IB1-tekst)                                                                                                                                                                                                                                                      |
| Sponsor | The sponsor is the party that commissions the organisation or performance of the research, for example a pharmaceutical company, academic hospital, scientific organisation or investigator. A party that provides funding for a study but does not commission it is not regarded as the sponsor, but referred to as a subsidising party. |
| SUSAR   | Suspected Unexpected Serious Adverse Reaction                                                                                                                                                                                                                                                                                             |
| WBP     | Personal Data Protection Act (in Dutch: Wet Bescherming Persoonsgegevens)                                                                                                                                                                                                                                                                 |
| WMO     | Medical Research Involving Human Subjects Act (in Dutch: Wet Medisch-wetenschappelijk Onderzoek met Mensen)                                                                                                                                                                                                                               |

## SUMMARY

**Rationale:** Guillain-Barré syndrome (GBS) is the most frequent cause of acute neuromuscular weakness in the Western world. GBS patients have a variable prognosis, 20-30% needs mechanical ventilation, 20% is unable to walk after 6 months and 3% dies. Using a simple scoring system it is possible to accurately predict which patient has a poor prognosis. GBS patients with a poor prognosis may benefit from a second course of IVIg.

**Objective:** To determine whether a second IVIg course in GBS patients with a poor prognosis improves functional outcome after 4 weeks. Secondary outcomes include functional outcome after 8, 12 and 26 weeks, mechanical ventilation, length of hospital and ICU admission, occurrence of TRF's, mortality and blood IgG levels.

**Study design:** A double-blind randomized placebo-controlled trial design will be used in selected patients with a poor prognosis. In patients with a good prognosis the study will have an observational design.

**Study population:** GBS patients of 6 years and older, who have an indication for IVIg treatment.

**Intervention:** Patients with a poor prognosis according to the prediction model (mEGOS) will be randomized to receive a second IVIg course or placebo.

**Main study parameters/endpoints:** The main study endpoint is functional outcome on the GBS disability scale 4 weeks after start of the first IVIg course. Other endpoints include functional outcome after 26 weeks.

**Nature and extent of the burden and risks associated with participation, benefit and group relatedness:** The participant will be physically examined at 7 standardized time-points, mostly in combination with the standard patient care. Extra blood and CSF (extra spinal tap is not requested) will be used for trial purposes. An EMG will be performed in the standard clinical work-up. A throat swab will be requested. Serious adverse effects of IVIg are rare (details in SPC). It is anticipated that also in children benefits will outweigh the risks of participating in this treatment trial. Standard treatment in children is the same as in adults, long-term prognosis is better as in adults; however 25% is still not symptom free at a median of 228 days in a large observational study.

## 1. INTRODUCTION AND RATIONALE

Guillain-Barré syndrome (GBS) is an immune mediated peripheral polyradiculoneuropathy characterized by rapid onset flaccid paresis and sensory disturbances with a very heterogenic distribution in clinical characteristics and in prognosis. Some patients develop mild limb paresis, whereas others develop oculomotor, facial, bulbar, respiratory muscle and limb paralysis and remain bed bound for several months. GBS is the most frequent cause of acute neuromuscular weakness in the Western world[1]. It affects 1.2 persons per 100,000 per year[2]. Intravenous immunoglobulin (IVIg) and plasma exchange (PE) are shown to be effective in patients with GBS[3-6]. These studies primarily assessed the proportion of patients that improved 4 weeks after onset of this treatment. Nowadays, IVIg (2 g/kg in 2-5 days) has become standard treatment for patients with GBS who are unable to walk unaided and still within the first 2 weeks from onset of weakness[4, 7, 8]. The outcome of GBS after 6 or 12 months however has not, or only marginally been improved[1, 6]. Approximately 20% are still disabled after 6 months, mechanical ventilation is needed in 20-30% and 3%-10% of the patients die. Patients with severe GBS and poor prognosis may need additional or more aggressive therapy to recover. Careful selection of patients eligible for extra therapy is important, because extra treatment entail added complication risk and costs. Multiple clinical, electrophysiology, serological and laboratory factors have been identified as predictors for poor outcome. These include older age[9-11], rapid disease progression[11], disability grade[10, 12, 13], preceding diarrhea/Campylobacter jejuni serology[9, 10, 12], absence of antecedent upper respiratory tract infection[12, 13], axonal EMG[12, 13] and anti-GM1 antibodies[14, 15]. A recent study showed that the prognosis of individual GBS patients can accurately be predicted based on three simple clinical factors that can easily be obtained early during the course of disease[10]. The selection of patients for the RCT phase of this SID-GBS study is based on this prognostic model.

GBS can affect persons at virtually every age, standard treatment for children is the same as for adults (2 g IVIg/kg administered in 2-5 days). A large prospective, multicenter study in children showed that only 75% was symptom free at last follow-up (median of 228 days)[16]. This underlines the importance of better treatment strategies, also in this subgroup of patients. Children of 6 years and older were also included in the two randomized controlled treatment trials on which the EGOS model was based[10]. Since it is likely that children potentially may also benefit from a second IVIg dose, we will include children from 6 years and older in this therapeutic study.

### **Rationale for the study**

There are several arguments suggesting that a second IVIg course can be effective in patients with a poor prognosis;

1. It is known that about 10% of GBS patients only have short-lasting improvement after a single IVIg course ('treatment-related clinical fluctuation'), a second dose of IVIg is then followed by functional improvement, suggesting that one IVIg course in these patients is insufficient [17]
2. A second course of IVIg is suggested to be effective in a small uncontrolled series of severe unresponsive GBS patients[18]

3. Additionally, recent data from our group show that patients with a relatively minor increase in serum IgG level after IVIg treatment recover significantly slower and fewer patients were able to walk unaided after 6 months (Kuitwaard, Ann Neurol in press).

Based on these findings, it is likely that at least a proportion of GBS patients may benefit from repeated courses of IVIg [6], especially the subgroup of patients with poor prognosis.

There are several arguments, however, for not treating all patients with a second IVIg course;

1. A proportion of GBS patients recover relatively well with the current treatment regime.
2. Thrombo-embolic (TE) complications are rare but are regularly described with the use of IVIg, most likely because of a rise in plasma viscosity [19-25]. A recent case-control study found that the risk of TE complications was elevated in patients with multiple cardiovascular risk factors[26]. Neurologic patients may be more prone to this complication because of their impaired mobility [20].
3. Presently the consumption of IVIg is increasing at an annual rate of 5% in Europe and 11% in the USA. A relative shortage of IVIg has been witnessed in recent years. In addition, IVIg is used in an off-label manner for nearly 100 conditions. High costs and limited resources will require targeted use of IVIg[21, 27].

We think it is justified to treat GBS patients with high risk of poor outcome with a second IVIg course because in those patients the benefits outweigh the risks.

### Erasmus GBS Outcome Scale (EGOS)

Recently, a prognostic model (EGOS) was developed that accurately predicts long-term outcome in GBS. The model was developed using a large number of GBS cases obtained from the Erasmus MC GBS databank, and the accuracy was confirmed in an independent large cohort of GBS patients[10]. One of the advances of the EGOS is that it needs only 3 simple and easy obtainable clinical features in the acute stage of GBS. Advanced age, presence of diarrhea  $\leq 4$  weeks before onset of GBS and high GBS disability score 2 weeks after start of first treatment were identified to be related with poor functional outcome after 6 months[10]. By using this simple and well-evaluated prognostic EGOS model, it is possible to select GBS patients with a poor prognosis that may benefit from a second IVIg dosage. Poor prognosis is defined as not being able to walk unaided (GBS disability score of 3 or higher).

### Advanced modified EGOS (mEGOS)

In the SID-GBS study we will use a modified version of the EGOS (table and figure 1).

| Table 1: The modified Erasmus GBS Outcome Score (mEGOS) chart. |            |        |
|----------------------------------------------------------------|------------|--------|
|                                                                | Categories | Score  |
| Age at onset (years)                                           | $\leq 40$  | 0      |
|                                                                | 41-60      | 1      |
|                                                                | $> 60$     | 2      |
| Diarrhoea ( $\leq 4$ weeks before onset of weakness)           | Absence    | 0      |
|                                                                | Presence   | 1      |
| MRC sumscore (1 week after entry)                              | 51 – 60    | 0      |
|                                                                | 41 – 50    | 3      |
|                                                                | 31 – 40    | 6      |
|                                                                | 0 – 30     | 9      |
| modified Erasmus GBS Outcome Score (mEGOS)                     |            | 0 – 12 |

In the modified version we will obtain data from the GBS patient 1 week after start of first IVIg treatment, because it is important to start a second course within the first 2 weeks of the illness when nerve damage might still be reversible. To construct the mEGOS we used the MRC sumscore (a score often used in GBS research) (table 4) at 1 week instead of the GBS disability score. The MRC sumscore consists of muscle force of 6 muscle pairs in both sides of the body, the MRC sumscore ranges from 0 (paralysis) to 60 (maximal muscle force). At one week (after onset of IVIg treatment) the MRC sumscore has a better predictive power than the GBS disability score. A second modification is that we will use the model to predict outcome at 4 weeks. A four week endpoint is usually the primary endpoint in clinical treatment trials in GBS. The GBS disability score is the scale generally used as outcome measure in GBS trials. Therefore we will use the GBS disability scale at four weeks as primary outcome in this trial.

[figure not shown]

Figure 1  
Predicted probability being able to walk at 4 weeks according to mEGOS. Patients with mEGOS 6-12 will be selected for randomization.

This mEGOS has a very good predictive power (Area Under the Receiver Operating Characteristic (ROC) Curve (AUC) = 0.87) for prediction of outcome after 4 weeks, indicating very good discriminative ability. In the patient group with a mEGOS of  $\geq 6$  (48% of total) 85% had a poor prognosis (being unable to walk unaided) after 4 weeks and 35% after 6 months (figure 2).

[figure not shown]

Figure 2  
Observed percentages in Erasmus GBS databank cohort (n=394) unable to walk after 4 weeks and after 6 months according to mEGOS.

Also mEGOS accurately predicts long-term outcome after 6 months of follow-up, with a good calibration (figure 3) and discrimination (AUC = 0.84).

[figure not shown]

Figure 3  
Calibration of the mEGOS model in the development data (n=394) for prediction of poor outcome after 6 months. The dotted line from 0.0 to 1.0 indicates perfect calibration. Triangles indicate the probabilities in grouped patients with similar predicted risks. A non-parametric, smoothed curve indicates the relation between predicted probability and observed frequency of poor outcome after 6 months.

Using mEGOS of six as a cutoff point we will select approximately 50% of patients. Those patients with a poor prognosis will be randomized to get a second IVIg course or placebo.

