### Hypothesis

GBS patients with the poorest prognosis (mEGOS 6-12) may benefit from a second course of IVIg when administered within the first weeks after onset of disease, when nerve damage is most likely still reversible.

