## 2. OBJECTIVES

### Primary objective

To determine whether a second IVIg dosage in GBS patients with a poor prognosis improve functional outcome after 4 weeks.

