### 3. STUDY DESIGN

A double-blind randomized placebo-controlled trial design will be used in selected patients with a poor prognosis. In patients with a good prognosis the study will have an observational design.

- All GBS patients in need of IVIg treatment, according to the treating neurologist, in a standard dosage of 2 g/kg in 2-5 consecutive days are potentially eligible for this study after obtaining informed consent.
- When patients sign 'Informed consent' they principally agree to be randomized to get a second IVIg dose or placebo when having a poor prognosis at day 7 and to be followed up for 6 months.
- Patients with the poorest prognosis based upon the modified EGOS (mEGOS 6-12) after the first IVIg course will be randomized to get a second course of IVIg (Nanogam®) in a dosage of 8 ml/kg (=0,4 g/kg) for 5 days or placebo (GPO®) in a dosage of 8 ml/kg for 5 days in a blinded fashion.
- mEGOS must preferentially be assessed 7 days after start of first IVIg course, with a range to 8 or 9 days. Trial medication needs then to be started within 24 hours when indicated according to the mEGOS score (see figure 4).
- Patient follow-up will be 6 months.
- Total patient inclusion will end when 44 patients with a poor prognosis received a second IVIg dosage.
- After covariate adjustment, to deal with variation between patients in baseline risk and to increase statistical power, data of the placebo group and the intervention group will be compared.

This is shown in the flowchart (table 2).

[figure not shown]

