### **4.2. Inclusion criteria**

#### **A. To enter this GBS study**

- Patients are diagnosed with GBS[30].
- There is an indication to start IVIg (irrespective of co-treatment with methylprednisolon (MP)) therapy:
  1. Patient is unable to walk unaided for >10 meter (grade 3, 4 or 5 of the GBS disability scale)
  - or
  2. There is otherwise an indication to start IVIg (with or without MP) treatment according to the treating neurologist.
- Onset of weakness due to GBS is less than 2 weeks ago.
- Signed informed consent.

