#### **B. To be randomized in the second IVIg dose phase (RCT), patients must fulfill the following criteria:**

- First IVIg (with or without MP) treatment with Nanogam® started within 2 weeks from onset of weakness.
- IVIg treatment has been 2g/kg administered in 2-5 days.
- Poor prognosis based upon the modified EGOS (mEGOS 6-12) at day 7 after start of first IVIg treatment.

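### The rationale wants the second IVIg course begun inside two weeks of onset, but the entry and timing rules allow a start from day 7 to day 24

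*Protocol*

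**What the plan says.** - **Rationale** (Protocol section 1, on the modified EGOS). EGOS uses the disability score 2 weeks after the start of first treatment. The modified score is taken at 1 week "because it is important to start a second course within the first 2 weeks of the illness when nerve damage might still be reversible".
- **Hypothesis** (section 1). Patients with mEGOS 6-12 "may benefit from a second course of IVIg when administered within the first weeks after onset of disease". No number of weeks is given.
- **Primary objective** (section 2). "To determine whether a second IVIg dosage in GBS patients with a poor prognosis improve functional outcome after 4 weeks". It sets no time window from onset.
- **Study entry** (section 4.2.A). "Onset of weakness due to GBS is less than 2 weeks ago".
- **Entry to the randomised phase** (section 4.2.B). The first course must have been "started within 2 weeks from onset of weakness", and poor prognosis is judged "at day 7 after start of first IVIg treatment". No criterion limits the time from onset to the second course.
- **Timing** (section 3). "mEGOS must preferentially be assessed 7 days after start of first IVIg course, with a range to 8 or 9 days". Then: "Trial medication needs then to be started within 24 hours when indicated according to the mEGOS score".
- **Analysis** (section 9). The covariate-adjusted model is written out with two terms, treatment and mEGOS. Section 7.1.3 lists the prognostic factors to correct for (age, preceding diarrhoea, serology, antibodies); time from onset is not among them. Section 7.2 allocates in blocks within each site.

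**The concern.** The 2-week figure is the stated reason for moving the score forward by a week, and it is the only number the protocol attaches to the period in which nerve damage may be reversible. The only limit on time since onset applies to the first course. The second follows at least a week later, so the late part of the permitted entry period cannot meet the rationale.

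What is at stake is interpretation. Randomisation keeps the treatment comparison valid whatever the time since onset. But if benefit does fall with time, as the reversibility argument suggests it might, the pooled estimate averages over patients inside and outside the 2-week window. A neutral result would then leave open whether a second course does not help or was often given later than the rationale intended.

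**Working it through.** **1. Range of start times.** Illness is taken to begin at onset of weakness, the only onset the entry rules use.

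Start of second course = (onset to first IVIg) + (first IVIg to mEGOS) + (mEGOS to trial medication)

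- Onset to first IVIg: 0 to 14 days (section 4.2)
- First IVIg to mEGOS: 7 to 9 days (section 3), or 7 only (section 4.2.B)
- mEGOS to trial medication: 0 to 1 day (section 3)

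Earliest: 0 + 7 + 0 = day 7. Latest: 14 + 9 + 1 = day 24, or 14 + 7 + 1 = day 22 with mEGOS strictly on day 7. The rationale's limit is day 14, so the rules can overshoot it by up to 10 days.

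**2. Who can meet the 2-week figure.** With mEGOS on day 7 and an immediate start, the first IVIg must begin by day 14 - 7 = 7. With mEGOS on day 9 and a start at 24 hours, it must begin by day 14 - 10 = 4.

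**3. Share starting after day 14.** The protocol gives no distribution of the delay from onset to first IVIg, so this rests on assumption. With delays cut off at 14 days, mEGOS on day 7 and trial medication uniformly 0 to 24 hours later:

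| Assumed delay | Mean after cut-off (days) | Start after day 14 |
|---|---|---|
| Exponential, mean 2 | 2.0 | 4% |
| Exponential, mean 4 | 3.6 | 17% |
| Exponential, mean 6 | 4.5 | 27% |
| Gamma, shape 2, mean 7 | 5.9 | 39% |
| Uniform, 0 to 14 | 7.0 | 54% |

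The uniform case can be checked by hand: the delay must exceed 7 - U, with U averaging 0.5, so the share is (7 + 0.5)/14 = 54%. If mEGOS were instead spread evenly over days 7, 8 and 9, the two extremes would become 7% and 61%.

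**4. Illustration of dilution, assuming no effect at all after day 14.** Section 4.4 takes 15% of controls able to walk at 4 weeks (85% unable), a 20-point gain, alpha 0.05 and power 0.80, and reports 145 poor-prognosis patients. The pooled two-sided formula reproduces this:

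n per arm = [1.96 × √(2 × 0.25 × 0.75) + 0.8416 × √(0.15 × 0.85 + 0.35 × 0.65)]² / 0.20² = 72.4, or 144.8 in total.

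If a fraction f starts after day 14 and gains nothing, the average gain is 20 × (1 - f) points. Power at 72.5 per arm is Φ{[d√72.5 - 1.96√(2p̄(1 - p̄))] / √(p₁(1 - p₁) + p₂(1 - p₂))}, with d = p₂ - p₁ and p̄ the mean of p₁ and p₂:

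| f | Rates compared | Gain (points) | Power |
|---|---|---|---|
| 0% | 15% v 35% | 20 | 80% |
| 10% | 15% v 33% | 18 | 72% |
| 20% | 15% v 31% | 16 | 63% |
| 30% | 15% v 29% | 14 | 53% |
| 50% | 15% v 25% | 10 | 32% |

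These figures use the protocol's unadjusted, dichotomous calculation. The planned main analysis is an ordinal proportional odds model in about 44 patients per arm, so they show direction and rough size only.

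**The case against.** The 2-week phrase is one hedged clause explaining a scoring change, and that change does bring treatment forward by about a week for every patient compared with scoring at week 2. The three arguments for a second course in section 1 (response to re-treatment after a fluctuation, an uncontrolled series, small IgG rises) are not tied to day 14. The protocol nowhere says that benefit stops then. Day 7 is the preferred scoring day, so day 24 is an outer limit. Rapid progression is listed in section 1 as a predictor of poor outcome, so patients with mEGOS 6-12 may reach treatment early. Finally, subgroup and interaction analyses are commonly left to a statistical analysis plan, which is not at hand, and section 9 foresees further exploratory work.

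Most of this stands, and it limits the point in three ways.

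- A reader might infer that many randomised patients will be treated outside the window. The documents do not show that, because the delay distribution is not given.
- A reader might infer that a null result could not be read against the hypothesis. That is too strong: the hypothesis has no numeric limit and the primary objective has no window, so a start on day 7 to 24 can satisfy both.
- The power losses depend on zero effect after day 14, which the protocol does not claim.

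The objection does not remove the mismatch. The hypothesis rests on the same reversibility argument as the rationale, and the 2-week figure is the only number given for it. A statistical analysis plan could add an analysis by time, but it could not reconcile the protocol's own passages.

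**Conclusion.** The protocol contradicts itself on timing. Its rationale calls for a start by day 14 of illness; its rules allow day 7 to day 24, or day 22 with strict day-7 scoring. Every patient whose first IVIg begins more than 7 days after onset falls outside the rationale's window. This follows from the text and needs no assumption beyond dating illness from onset of weakness.

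The practical size is uncertain. The late share is unknown; about 4% to 54% is a range over assumed delays with mEGOS on day 7, not an estimate. The dilution table is an illustration under an extreme assumption. A neutral trial would count against the hypothesis as written, and would be ambiguous only against the narrower 2-week rationale. The mismatch should be corrected, but it does not threaten the validity of the randomised comparison.

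**What to change.** 1. Reconcile the rationale and hypothesis in section 1 with the timing rule in section 3 and the criteria in section 4.2, so that all state the same intended window from onset of weakness to the second course. Which window to adopt, and whether entry should change, is for the sponsor.
2. In section 9, add days from onset of weakness to randomisation (T) to the adjusted proportional odds model for the randomised comparison, so that its linear predictor has terms for treatment, mEGOS and T. T is fixed at baseline and exists for every randomised patient, dosed or not. Time to start of trial medication should not be used, because it is determined after randomisation.
3. Pre-specify one treatment-by-T interaction, with T continuous, in a separate model labelled supportive.

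The onset date is already needed to apply the entry rules, and the randomisation date arises when the patient is registered, so no patients or procedures are added. The cost is protocol wording and one more model term. With about 44 per arm the interaction will have low power: it can describe how the effect varies with time but is unlikely to settle the reversibility question.
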